**Fig. 1 Fig1:**
[figure not shown]
Flow chart of the ‘cycle at work’ study

The study protocol has been registered at the International Standard Randomised Controlled Trial Number (ISRCTN11584275).

The Standard Protocol Items: Recommendations for Intervention Trials reporting guidelines were used to guide the preparation of this pilot study protocol [72].

#### Participants

Participants will be office-based employees from two professional companies in Dublin, Ireland.

##### Inclusion criteria

Males who spend most of their working week performing desk-related activities

##### Exclusion criteria

Have limitations with or contraindications to physical activity as indicated by the Physical Activity Readiness Questionnaire [73]Do not have a personal deskFemalesAge under 18 yearsEmployees who plan to be absent from the workplace for more than 2 days during the study periodEmployees who are involved in another programme or intervention to reduce behaviours

#### Randomisation

Following baseline assessments, worksites will be randomised to the intervention or control arms of the trial. Simple cluster randomisation will be determined by a statistician not associated with the project, who will use randomisation software to allocate each worksite to begin with either the intervention or control period.

#### Allocation concealment

Participants will not be advised of their group allocation until after baseline assessments have been made. The allocation concealment mechanism is important to reduce selection bias as it prevents foreknowledge of the period (control/intervention) in which participants are enrolling, which negatively affect recruitment [74].

#### Blinding

Due to the nature of the study, neither the participants nor the research team will be blinded to group assignments.

#### Setting and context

The proposed randomised pilot feasibility study will be conducted in two private-sector professional organisations in Dublin, Ireland (a legal firm and an online medical education provider). The sites have been chosen to target professional males as outlined in the introduction as those with the highest risk of prolonged SB.

Management approval has been obtained for employee recruitment, for permission to make environmental changes in the office setting, and for study contacts to occur during work-time. All participants will provide written informed consent before inclusion in the study.

#### Selection and recruitment

Convenience sampling has been used to recruit the organisations who have been involved in the development of this pilot study. The organisations were initially approached through the lead researcher’s personal networks. Purposive sampling will be used to recruit eligible participants in the companies via an email sent by a contact within each company. Participants in this study will include members of management and managing partners as well as employees.

#### Sample size

No formal sample size calculations are produced for this pilot feasibility study. The sample size is pragmatic and chosen based on resources. Thirty male desk-based workers will be recruited to the feasibility trial. A sample size of *n* = 30 is conventionally deemed adequate for pilot studies as it permits collection of sufficient useful data while minimising research costs [75].

Focus groups comprising separate management and employee participants in each worksite will be recruited (four in total) for intervention evaluation purposes. This is appropriate in qualitative research of this kind, with diversity of sampling (i.e. all stakeholder groups) more important than numbers of focus groups [76].

#### Procedure

An open call will be given to all staff who meet inclusion criteria, regardless of area/department to take part in the research. When preliminary agreement to the study has been obtained, the lead researcher will meet potential participants at their workplace, where they will be provided with a consent form, participant information leaflet (PIL), and a verbal explanation of the study. Participants who are interested in taking part in the study will be asked to consider the consent form and PIL for a 24-h period. Arrangements to meet all participants who are willing to participate will then be made, and they will then sign the consent form. The Physical Activity Readiness Questionnaire (rPARQ) health screening tool [73] will be administered to participants at the information/briefing stage to ensure participants’ physical capability to safely participate in the study.

Following the baseline period, all participants will be provided with a report via email on their weekly SB and PA derived from their baseline accelerometer data. Participants randomised to the intervention group will then be shown by the lead researcher in a face-to-face session at their workplace on the correct use of the intervention equipment. The goal of cycling 30–40 min/day (i.e. ≥ 5 min/h for 8 h) has been chosen as the minimum amount of exercise break to fractionate SB [31]. The Garmin watch is paired with a Bluetooth cadence sensor on the pedal machine and will record minutes of cycling upon start and stop buttons pressed by participants. The completed activity will transfer wirelessly via Bluetooth to a smartphone application (Garmin Connect) or to the website on participants’ workplace computer using a wire. The watch has a ‘move bar’ that visually appears and provides a sound and vibration alert after 1 h of inactivity. Additional segments appear every 15 min of inactivity thereafter. The move bar is reset by engaging in a small amount of physical activity (i.e. work short distance, record stationary cycling). The Garmin platform does not allow the setting of SB goals, but does allow cycling-time goals. Prior to the intervention commencement, all participants will be assigned teams formed within sites (e.g. managers versus employees, or a mix of roles), which will target the social comparison behaviour change strategy. The Garmin platform allows self-monitoring of participants’ own time spent in SB, PA, and cycling, and participants will be encouraged to visit the site regularly. A weekly email from the researcher will provide encouragement and feedback on participants’ activity progress. For logistical and practical reasons, there will be a buffer week after randomisation. This is to allow the researcher to attend the workplaces to deliver the pedal machines and Garmin watches.

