The intervention comprises the provision of the following components: (1) an under-desk portable pedal machine (DeskCycle2; 3D Innovations LLC., Greeley, CO, USA), (2) Garmin Forerunner 35 activity tracker, and (3) access to a Garmin Connect application (app) and website (Garmin.com). The organisational-level component will be targeted by recruiting management staff to the study, thereby garnering support for employees to participate in the pilot study.

The intervention will communicate the key message: ‘cycle at work’. As highlighted from prior qualitative work, the determinants goal-setting, self-monitoring, and social comparison will be included using BCTs provided within the Garmin Connect app/website. Gender-sensitised interventions that recognise men’s interests and tailor health promotion efforts for this specific group have been found to be more effective in increasing physical activity [68, 69]. Social comparison will be used as a strategy to focus on the masculine ideal. By engaging men in PA, this draws upon as well as provides opportunities to garner masculine capital by affirming competitiveness and/or striving for physical prowess [68, 70]. Social comparison will be targeted by providing weekly feedback of each team’s progress. Participants will also be prompted to move every 60 min of accumulated SB using the ‘move’ prompt on the Garmin Forerunner 35 wrist-worn device.

Figure 1 shows an overview of the study timeline. The intervention and control arms will be conducted over 14 days each. The active intervention will involve the use of an under-desk pedal machine to interrupt SB every hour and accumulate ≥ 30 min of cycling time during the working day. There will be a washout period of 1 week between the intervention and control arms. The washout period is used as there is a possibility that the effect of a treatment/intervention in one period may carry over into the next period [71]. These are known as carryover effects. Unless both carryover and period effects are known to be negligible, a crossover design loses its advantages. In order to ensure negligible carryover effects, there is a need to have sufficient washout periods between intervention periods. In circumstances where a participant suffers any adverse outcome such as pain or discomfort while taking part in the study, they will be advised to immediately discontinue participation in the study and to contact their doctor.

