#### Assessments

At baseline, participants will wear the thigh-based accelerometer (activPAL3) monitor for 24 h/day, for nine consecutive days (and 14 days each for control and intervention arms). All device removals will be documented in a wear diary. Prior to being attached to the participant, the device will be set to record at 20 Hz. The activPAL3 will be set to start recording at 0001 h on the day after the participant receives the device. Each device will be attached to the anterior aspect of the midline of the right thigh using a nitrile sleeve and waterproof Tegaderm dressing. Sleep, sedentary time, standing time, physical activity (i.e. stepping time (minutes) (cadence ≥ 100, duration > 1 min) will be derived from the activPAL3 data. An acceleration threshold has been developed (unpublished data) to identify under-desk cycling, i.e. cut-point threshold acceleration exceeding 375.0 (sum of vector magnitude), while seated (recorded as SB by activPAL), and in bouts lasting ≥ 5 continuous minutes. Only cycling that occurs within self-reported working hours will be analysed and then quality-checked by comparing to user-entered Garmin recorded cycling time. Sedentary time and standing time will be calculated using the postural function of the monitor through the associated software (activPAL v8.10.8.75).

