##### Protocol adherence criterion

Green—≥ 80% of participants engage in > 60% of their cycling goal

Amber—60–79% of participants engage in > 60% of their cycling goal

Red—<60% of participants engage in > 60% of their cycling goal

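### The cycling goal behind the adherence progression criterion is stated inconsistently, so its 60% cut is either more than 18 or more than 24 minutes a day

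*Protocol article*

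**What the plan says.** All places are in the Protocol article.

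- **Intervention development process:** participants are to "interrupt SB every hour and accumulate ≥ 30 min of cycling time during the working day". This is a daily total with a floor of 30 min and no minimum bout length.
- **Procedure:** "The goal of cycling 30–40 min/day (i.e. ≥ 5 min/h for 8 h"). The text describes this as a minimum amount. The same section says that the Garmin watch, paired with a cadence sensor on the pedal machine, records cycling minutes when the participant presses start and stop.
- **Assessments:** under-desk cycling is identified from the activPAL signal above an acceleration threshold, "while seated (recorded as SB by activPAL), and in bouts lasting" at least 5 continuous minutes. Only cycling within self-reported working hours is analysed, and Garmin time serves as a quality check on it.
- **Protocol adherence criterion:** the top band reads "Green—≥ 80% of participants engage in > 60% of their cycling goal". The two lower bands apply the same test to each man: a share from 60% to 79% is Amber, and anything lower is Red. Neither the goal in minutes nor the measure is named here.
- **Progression criteria:** the criteria are to be read as guidelines and not as strict thresholds. Red nevertheless means that a full trial will not be considered unless there are clear extenuating circumstances.

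**The concern.** Adherence is one of only two progression criteria given with colour bands; the other is retention. Its denominator is the cycling goal, and the article's statements of that goal do not reduce to one number. The floor of 30 and the range of 30–40 share a lower bound. The hourly rule, which the Procedure section presents as the same thing as the range, does not share it.

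If the goal is left open, the colour depends partly on which statement the analyst picks, and that choice could be made after the cycling data are known. A reader of the results could not tell whether a Red or Amber reflects the men's use of the machine or the choice of denominator.

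A second, conditional matter concerns the numerator. If adherence is scored with the activPAL detector, bouts shorter than 5 continuous minutes count as zero, although the Intervention development process section speaks of minutes being accumulated over the day.

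**Working it through.** **Inputs from the article.** Goal of at least 30 min per working day (Intervention development process); goal of 30–40 min/day, equated with at least 5 min/h for 8 h (Procedure); pass mark of more than 60% of the goal, with bands at 80% and 60% of participants (Protocol adherence criterion); 30 participants (Sample size); detector minimum of 5 continuous minutes (Assessments).

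**Step 1: the plan's own figure.** 5 min/h × 8 h = 40 min. With the at-least sign, this is a floor of 40, not a range of 30–40. A total of 30 min corresponds to 30 / 5 = 6 h at that rate.

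**Step 2: the cut.** Cut = 0.60 × goal, strictly exceeded.

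- Goal 30: 0.60 × 30 = 18 min/day.
- Goal 35 (midpoint of the range): 0.60 × 35 = 21 min/day.
- Goal 40: 0.60 × 40 = 24 min/day.

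**Step 3: the bands in numbers of men.** With 30 participants, Green needs 0.80 × 30 = 24 or more, Amber is 18 to 23 (0.60 × 30 = 18), and Red is 17 or fewer.

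**Step 4: the extreme case.** If every man averages 20 min/day, 30/30 exceed 18 (Green) and 0/30 exceed 24 (Red). The same split arises at any common level above 18 and up to 24 min/day.

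**Step 5: with spread between men.** The article gives no distribution of cycling time. Assume average daily minutes are normal with mean m and SD s, so that the share above cut c is 1 − Φ((c − m)/s).

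| Assumed mean, SD | Share above 18 | Share above 24 |
|---|---|---|
| 20, 10 | 1 − Φ(−0.20) = 58%, Red | 1 − Φ(0.40) = 34%, Red |
| 22, 3 | 1 − Φ(−1.33) = 91%, Green | 1 − Φ(0.67) = 25%, Red |
| 22, 4 | 1 − Φ(−1.00) = 84%, Green | 1 − Φ(0.50) = 31%, Red |
| 22, 8 | 1 − Φ(−0.50) = 69%, Amber | 1 − Φ(0.25) = 40%, Red |
| 24, 6 | 1 − Φ(−1.00) = 84%, Green | 1 − Φ(0.00) = 50%, Red |
| 25, 10 | 1 − Φ(−0.70) = 76%, Amber | 1 − Φ(−0.10) = 54%, Red |
| 28, 10 | 1 − Φ(−1.00) = 84%, Green | 1 − Φ(−0.40) = 66%, Amber |
| 30, 4 | 1 − Φ(−3.00) = 99.9%, Green | 1 − Φ(−1.50) = 93%, Green |

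With a wide spread the colours differ by one band or agree. Green against Red needs cycling clustered near 18–24 min/day. If cycling is well above or well below that interval, the choice of goal does not matter.

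**Step 6: the numerator, only if the detector is used.** Eight bouts of 5 min make 40 min and count in full. Eight bouts of 4 min make 8 × 4 = 32 min, above both cuts, but the detector counts 0. These are two chosen patterns. The article says nothing about how long bouts will actually be.

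**The case against.** **The goal statements largely agree.** A floor of 30 and a range of 30–40 described as a minimum are compatible, and only the parenthesis departs from them. This is right as far as it goes, and it narrows the conflict to the hourly rule. It does not remove it, because the article presents the range and the hourly rule as equivalent and the criterion does not say which one applies. Their cycling goal might also mean a goal set on the Garmin platform, which allows cycling-time goals; that would leave the denominator no more fixed.

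**A reader might infer that the same behaviour will generally score Green on one goal and Red on the other.** The article does not support that. It gives no distribution of cycling time, and with an assumed SD of 10 the two examples at means of 25 and 28 move by one band.

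**A reader might infer that adherence is scored on the detector and that its 5-minute rule is a flaw.** The adherence criterion names no device. The Assessments section makes detector time the analysed cycling measure, which supports the inference without settling it. The bout minimum matches the hourly instruction, so a man who follows that instruction is counted in full. The threshold rests on unpublished data, so whether the minimum is needed to separate pedalling from other seated movement cannot be judged here.

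**A reader might infer that Garmin minutes should replace the detector.** They depend on participants pressing start and stop, in an unblinded study with team comparison and weekly feedback. Keeping the accelerometer first is defensible.

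**The criteria are guidelines.** This stands and lowers the severity. A guideline still needs a defined denominator, and Red carries a presumption against progression.

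**Conclusion.** The point holds for the denominator. The stated range does not reproduce from the hourly rule equated with it (at least 40 min against 30–40), and the adherence cut is therefore more than 18 or more than 24 min/day. That much follows from the article's figures alone.

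The effect on the colour rests on assumed cycling distributions. One band is plausible when many men cycle about 18–24 min/day. Green against Red requires tight clustering in or near that interval. Outside it there may be no effect. The calculations also assume that adherence is judged on each man's average per working day.

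The numerator point is conditional on the detector being the scoring measure and is a reason for a sensitivity result, not a defect shown. Overall this should be fixed, but it falls short of a must-fix because the Progression criteria section asks for judgement and allows for extenuating circumstances.

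**What to change.** 1. Reconcile the Intervention development process and Procedure sections to one daily cycling goal. Which goal is for the sponsor to decide.
2. In the Protocol adherence criterion, state the cut as a fixed number of minutes per working day, derived from that goal, before any cycling data are seen.
3. Name the measure used to score the criterion.
4. If that measure is the activPAL detector, also report the criterion on Garmin cadence-sensor minutes in working hours as a sensitivity result, and note that these depend on participants pressing start and stop. Garmin need not become the primary measure, and the 5-minute bout minimum need not be removed.

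The cost is a few lines of protocol wording and one further tabulation of data that the study already collects. No procedure or sample size changes.

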#### Control arm

Participants in the control arm will be informed that they have been randomised to a delayed intervention that will begin after 3 weeks and will be asked to continue their normal workplace habits. All measures collected in the intervention group will be collected in the control arm.

#### Assessments

At baseline, participants will wear the thigh-based accelerometer (activPAL3) monitor for 24 h/day, for nine consecutive days (and 14 days each for control and intervention arms). All device removals will be documented in a wear diary. Prior to being attached to the participant, the device will be set to record at 20 Hz. The activPAL3 will be set to start recording at 0001 h on the day after the participant receives the device. Each device will be attached to the anterior aspect of the midline of the right thigh using a nitrile sleeve and waterproof Tegaderm dressing. Sleep, sedentary time, standing time, physical activity (i.e. stepping time (minutes) (cadence ≥ 100, duration > 1 min) will be derived from the activPAL3 data. An acceleration threshold has been developed (unpublished data) to identify under-desk cycling, i.e. cut-point threshold acceleration exceeding 375.0 (sum of vector magnitude), while seated (recorded as SB by activPAL), and in bouts lasting ≥ 5 continuous minutes. Only cycling that occurs within self-reported working hours will be analysed and then quality-checked by comparing to user-entered Garmin recorded cycling time. Sedentary time and standing time will be calculated using the postural function of the monitor through the associated software (activPAL v8.10.8.75).

Contextual SB information will be measured using self-report via Ecological Momentary Assessment (EMA). The use of EMA has been recommended to collect ecologically valid and context-specific outcome data alongside objective measures in studies [77, 78]. EMA involves repeated sampling of participants’ current behaviours and experiences in real time and in their natural environments. This is useful to specify the type of activity or contextual factors (e.g., physical, social, temporal, affective) surrounding these behaviours which are important factors to consider when developing interventions and that cannot be provided by objective measures [79]. EMA has been reported as a valid and reliable measure of SB and PA in adults [80] and for use in a workplace setting [81]. Each day, six notifications will appear on participants’ own mobile smartphones at random times between 8 am and 10 pm, using the application PIEL Survey (pielsurvey.org, v1.2.4.2). The notifications are scheduled at random times to obtain a representative sample of participants’ activities over the course of their study participation. The questions have been found to be valid and feasible [82].

Work engagement will be measured at baseline, post-control arm, and post-intervention arm using the Utrecht Work Engagement Scale (UWES-9) [83]. The perceived benefits of reducing SB in the workplace will also be assessed at these time points using a questionnaire devised by the research team. Immediately upon finishing the study, participants will be asked to complete a questionnaire to assess the acceptability, appropriateness, and feasibility of the intervention [63].

Focus groups and semi-structured interviews will be carried out within the 2-week post-intervention follow-up. An interview schedule has been designed based on existing literature. The interview schedule for the focus groups will be guided by Orsmond et al. [84]. The schedule will be pre-piloted on a small number of employees within the author’s place of work, within the Discipline of Public Health and Primary Care.

#### Pilot outcomes

Trial-related outcomes will be explored within the focus groups and/or semi-structured interviews which includes:
Acceptability of the assessments and burden by the users—from a management and employee perspectiveAcceptability of the study procedures by the users—from a management and employee perspective

##### Recruitment and retention

Number of people recruited to the study recorded by the researcher at the beginning of the studyNumber of dropouts in the study will be recorded

##### Feasibility of measurement tools

Missing data from questionnaires. This information will be recorded by the researcher in a separate report at the end of the study.

##### Potential intervention effectiveness

Trial-related outcomes will be assessed at baseline (before randomisation) and throughout the control and intervention periods:
SB and PA measured using ActivPal3 accelerometers:

-SB in minutes during working hours (workplace SB) and all waking hours (total SB)

-PA in minutes during working hours (workplace PA) and all waking hours (total PA)
Context-specific SB measured using EMA with notifications of survey completion sent six times a day at random times throughout the baseline, control, and intervention armsWork engagement will be measured at baseline, post-control arm, and post-intervention arm using the UWES-9 [85] using pen and paperPerception of the benefits of reducing workplace SB will be assessed using the 3-point questionnaire at baseline and immediately post-intervention using pen and paper

